# Patient-reported outcome after stemmed versus stemless total shoulder arthroplasty for glenohumeral osteoarthritis: a patient-blinded randomized clinical trial

**DOI:** 10.1186/s13063-019-3535-9

**Published:** 2019-07-12

**Keywords:** Shoulder arthroplasty stemless, Non-stemmed, Shoulder prosthesis, Shoulder replacement, Shoulder osteoarthritis, Metaphyseal fixation

## Abstract

**Background:**

Stemless shoulder arthroplasty systems with uncemented metaphyseal fixation have been used for glenohumeral osteoarthritis since 2004 (Hawi, et al. BMC Musculoskelet Disord 17:376, 2016). The stemless design has several theoretical advantages compared with the stemmed shoulder arthroplasty systems: restoring patients’ anatomy; preserving humeral bone stock; and few complications in component removal if the need for a revision arthroplasty arises. The purpose of the study is to compare the short-term, patient-reported outcome of stemless and stemmed total shoulder arthroplasty (TSA).

**Materials and methods:**

A randomized clinical trial will be conducted. Eighty patients with clinical and radiological signs of primary or post-traumatic glenohumeral osteoarthritis, computed tomography (CT) scan-verified adequate glenoid bone stock, and no total rupture of rotator cuff tendons verified by a magnetic resonance imaging (MRI) scan will be randomly allocated to a stemless or stemmed TSA. The primary outcome will be the Western Ontario Osteoarthritis Shoulder (WOOS) score at 12 months. Secondary outcomes are the WOOS score at three months and the Oxford Shoulder Score (OSS) and EQ-5D at 3 and 12 months. All complications, including glenoid and humeral component loosening, instability, rotator cuff tear, intraoperative and postoperative periprosthetic fracture, nerve injury, infection, deltoid injury, and symptomatic deep venous thrombosis, will be reported.

**Discussion:**

Findings will provide patients with better information about the potential benefits and harms of stemless and stemmed TSA and will assist shoulder surgeons and patients in decision-making.

**Trial registration:**

Clinicaltrials.gov, NCT03877315. Registered on 13 March 2019.

**Electronic supplementary material:**

The online version of this article (10.1186/s13063-019-3535-9) contains supplementary material, which is available to authorized users.

## Background

Glenohumeral joint osteoarthritis is a common cause of shoulder pain, affecting up to one-third of patients aged > 60 years [1]. Surgical treatment is indicated for patients with glenohumeral arthritis who continue to experience significant symptoms despite an appropriate course of non-operative management. Shoulder arthroplasty accounts for the third most common joint replacement procedure after hip and knee arthroplasty [2]. Based on data from the National Patient Registry, the Statistical Department of the Danish National Board of Health, the use of primary shoulder replacement in Denmark increased from 12 replacements per 100,000 inhabitants in 2005 to 19 replacements per 100,000 inhabitants in 2015 [3]. Glenohumeral osteoarthritis is now the most common indication for total shoulder arthroplasty (TSA) in Denmark [3].

Many different TSA designs are available on the market. The stemless shoulder arthroplasty system with uncemented metaphyseal fixation has been used in Europe for glenohumeral osteoarthritis since 2004. The indications for anatomical stemless TSA are the same as for anatomical stemmed TSA: osteoarthritis; rheumatoid arthritis; and post-traumatic osteoarthritis or osteonecrosis.

The contraindications for anatomical stemless TSA are acute proximal humerus fracture, inadequate metaphyseal bone stock, and rotator cuff insufficiency [4, 5].

Stemless TSA has several theoretical advantages over stemmed TSA: restoring patients’ anatomy (humeral shaft angle, humeral head diameter, and lateralization); preserving humeral bone stock; and few complications in component removal should the need of a revision arthroplasty arise [6–8]. A recent review of 3360 anatomical TSAs found an overall complication rate of 10.3% [8]. Periprosthetic fractures accounted for 6.7% and humeral component loosening for 1.4% of all complications. Complications related to the stemmed humeral component can be divided into intraoperative (malpositioning, false route, periprosthetic fracture) and postoperative (loosening, migration, disassembly, periprosthetic fracture, stem fracture) complications [9]. When a revision is necessary because of infection or periprosthetic fracture, the removal of a well-fixed or cemented humeral component can be challenging and lead to bone damage [10].

Few outcome studies on stemless TSA are available. A recent review of 11 observational studies (published 2010–2016), incorporating a total of 929 patients, reported comparable short- and mid-term functional outcomes between stemmed and stemless shoulder prosthesis [11]. Otherwise, there are few well-conducted and adequately powered clinical studies.

The objective of this study is to increase knowledge about shoulder function after operation with anatomical TSA by comparing the patient-reported outcome after stemmed and stemless anatomical TSA for glenohumeral osteoarthritis.

The Standard Protocol Items Recommendations for Interventional Trials (SPIRIT) Statement 2013 has been followed for the completion of this protocol (Table 1 and Additional file 1).

**Table 1 Tab1:**
[figure not shown]
Standard Protocol Items Recommendations for Interventional Trials (SPIRIT) diagram

*Stemmed group* patients operated with stemmed shoulder arthroplasty, Biomet Comprehensive® Total Shoulder System, *Stemless group* patients operated with stemless shoulder arthroplasty, Biomet Comprehensive® Nano Shoulder System *WOOS* Western Ontario Osteoarthritis Shoulder, *OSS* Oxford Shoulder Score, *EQ-5D* the health status component of the EuroQol assessment

## Methods/Design

### Study design

An investigator-initiated, blinded (patient and data analyzer), non-inferiority, randomized controlled clinical trial.

### Material

Seventy-eight patients with shoulder osteoarthritis randomized to either stemmed or stemless shoulder prosthesis. The flow of participants into the study are demonstrated in Fig. 1

**Fig. 1 Fig1:**
[figure not shown]
CONSORT 2010 *flow diagram*. The expected flow of patients through the study. TSA total shoulder arthroplasty

### Inclusion criteria

Patients aged ≥ 18 years.Patients have been referred to the Orthopedic Department or Zealand University Hospital, Koege or Hvidovre University Hospital for shoulder pain during the study period.Patients have the ability to read trial information in Danish and give informed consent.The diagnosis will be based on plain radiographs (at least two perpendicular views), reduction of joint space, and/or osteophyte formation.Clinical presentation with pain at night and/or daily pain, pain in overhead activity, and consumption of pain medication.

### Exclusion criteria

Previous shoulder surgery that involves the humeral head and/or the glenoid cavity.Patients with alcohol or drug abuse problems that can compromise rehabilitation and follow-up appointments as assessed by the recruiting surgeon at the first visit.Patients unable to understand instructions in Danish, follow the rehabilitation protocol, or answer the questionnaires because of physical or cognitive inabilities as evaluated by the recruiting surgeon at the first visit.Brachial plexus palsy.Patients with previous fractures around the shoulder (clavicle, scapula, and proximal humerus fractures).Patients with magnetic resonance imaging (MRI) scan-verified full thickness total tear of one or more of the rotator cuff tendons.Patients with computed tomography (CT) scan-verified glenoid retroversion ≥ 20° that does not allow glenoid component fixation without bone graft or need an augmented glenoid component [12].

### Eligibility

Patients referred with the diagnosis of “glenohumeral osteoarthritis” will be examined by clinical examination and plain radiographs to confirm the diagnosis. In the case of glenohumeral osteoarthritis, which is to be treated with TSA, the shoulder surgeon will offer the patient participation in the trial at the first visit; the patient will be referred to routine shoulder CT and MRI scans (which are already a part of standard shoulder osteoarthritis protocol) and receive a folder with patient participant information and “Researchers rights in a health science research project.”

Patients will have time to consider participation before the next visit (approximately one month) after the first visit.

At the second visit, if the patients give their informed consent for participation in the study, they will receive three questionnaires to fill out while undisturbed in a room next door before handing them to a secretary who will check that the questionnaires are completed before the patient leaves the hospital.

The informed consent gives the primary investigator access to information about the patient’s health condition from the medical record, including data on age, sex, American Society of Anesthesiologists (ASA) score, previous shoulder operations, and results from shoulder CT and MRI scans.

All surgical interventions will be undertaken at the Zealand University Hospital Koege and Hvidovre Hospital. A two-year recruitment period from 01 March 2019 to 01 January 2022 is planned.

### Randomization and concealment of allocation

A computerized irreversible randomization application, Research Electronic Data Capture (REDCap)© [13], will allocate patients into two equal groups:Operated with stemmed shoulder arthroplasty, Biomet Comprehensive® Total Shoulder System; andOperated with stemless shoulder arthroplasty, Biomet Comprehensive® Nano Shoulder System.

The randomization sequence will be computer-generated by block randomization (four in each block) and balanced according to age in years (18–49, 50–59, 60–69, 70–79, 80–89, 90–110), sex, and ASA score. The randomization (patient allocation) will be performed on the trial laptop computer in the operation room while the patient is being anesthetized in the preparation room next door. The operating surgeon will obtain the allocation code by logging onto the REDCap website after positioning the anesthetized patient in a beach chair position. After randomization, the patient’s allocation will be revealed to the operation team to unpack the necessary operation tools and prosthesis.

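### A fixed, published block of four, drawn and seen by unblinded operating surgeons, leaves some later allocations predictable; varying, undisclosed block sizes would remove most of this cheaply

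*Protocol article*

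**What the plan says.** All of the following is in the protocol article, mainly under Randomization and concealment of allocation.

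- Block length: "The randomization sequence will be computer-generated by block randomization (four in each block". No variation in block size is mentioned, and the ratio is 1:1 (REDCap "will allocate patients into two equal groups").
- Balancing: the sequence is "balanced according to age in years (18–49, 50–59, 60–69, 70–79, 80–89, 90–110), sex, and ASA score". The text does not say whether each combination has its own blocks, or how many ASA levels are used. Hospital is not listed as a factor.
- System: "A computerized irreversible randomization application, Research Electronic Data Capture (REDCap".
- Who draws: "The operating surgeon will obtain the allocation code by logging onto the REDCap website after positioning the anesthetized patient in a beach chair position".
- Who sees the result: "the patient’s allocation will be revealed to the operation team to unpack the necessary operation tools and prosthesis".
- Timing: the same paragraph also has the randomization "performed on the trial laptop computer in the operation room while the patient is being anesthetized in the preparation room next door".

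Elsewhere, Study design blinds only the patient and the data analyzer, Interventions names four operating surgeons, and Eligibility names two hospitals. Some exclusions rest on judgement, for example: "Patients with alcohol or drug abuse problems that can compromise rehabilitation and follow-up appointments as assessed by the recruiting surgeon at the first visit".

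**The concern.** With a known block of four at 1:1, anyone who has followed a block can work out its end. A late draw does not prevent this, because the inference comes from earlier allocations and not from opening the next code. Age, sex and ASA are known before surgery, so a surgeon also knows which stratum the next patient belongs to.

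The place in the sequence is taken at surgery, not at consent. The usable decisions are therefore the order of patients on the theatre list and a late decision not to proceed. The two descriptions of the draw, during anaesthesia next door and after positioning, leave the last point for holding back a case undefined.

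There is a conceivable reason to steer. Background lists inadequate metaphyseal bone stock as a contraindication to the stemless implant, while the inclusion and exclusion criteria contain nothing on humeral bone stock. The Discussion relies on randomization to avoid selection bias. If cases were steered, the comparison would carry a bias that the planned analysis could not remove.

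**Working it through.** **The plan's own figure.** The article gives no predictability figure. Its sample size sets the N used here. With margin 12.5, SD 20.0, one-sided alpha 0.05 and power 80%, n per arm = 2 × (1.645 + 0.842)² × 20² / 12.5² = 31.7, so 32 per arm and 64 in total, as stated. Then 32 × 1.2 = 38.4, so 39 per arm, which gives the stated 78.

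**One unstratified sequence, known in full.** There are six possible blocks of four.

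- Probability that the allocation is certain at positions 1 to 4: 0, 0, 1/3, 1. Mean = (1/3 + 1)/4 = 33%.
- Best-guess accuracy at positions 1 to 4: 0.5, 0.667, 0.667, 1. Mean = 70.8%, against 50% by chance.

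**Blocks within strata.** The balancing factors give 6 age bands × 2 sexes × ASA levels. With 2 to 4 ASA levels (assumed) there are 24 to 48 strata. If equal in size, they average 78/24 = 3.3 down to 78/48 = 1.6 patients, so many blocks never reach positions 3 and 4, where certainty arises. Simulations of 78 patients with separate blocks of four per stratum, and block starts assumed known, gave:

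- *Every earlier allocation in the stratum known, uneven case mix* (age 3/12/33/40/11/1%, 60% female): 23.9%, 20.9% and 20.3% certain with 2, 3 and 4 ASA levels; best guess right 65–66% of the time. A second mix (age 1/9/30/42/17/1%, sex 40/60%, ASA 12/63/25%) gave 21.7% and 65.5%.
- *Same knowledge, equal strata*: 20.0%, 13.7% and 9.5% certain for 24, 36 and 48 strata; best guess 60–65%.
- *Own hospital's allocations only, sequences common to both hospitals, second mix*: about 5% certain.
- *Own cases only, one of four surgeons*: about 1–2% certain. If sequences were split by hospital (not stated) with two surgeons at each, about 3–4%. With that split, full knowledge gives about 14–18%.

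**In patients out of 78.** 0.10 × 78 ≈ 8 and 0.24 × 78 ≈ 19 with full knowledge; 0.05 × 78 ≈ 4 with own-hospital knowledge; 0.01 × 78 ≈ 1 to 0.04 × 78 ≈ 3 with own cases only.

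**Effect of varying the blocks.** Under full knowledge, with block sizes varying at random over a set that includes six, the certain share falls from about 22% to about 1–4%. Best-guess accuracy stays near 65%.

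**The case against.** Three stronger readings are tempting, and the article supports none of them.

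- *The surgeons who recruit are the ones who draw.* With four operators this is plausible. But the article speaks separately of a recruiting surgeon, a shoulder surgeon who offers the trial and an operating surgeon, and never says that they are the same people.
- *A third of allocations are known in advance.* That needs a single unstratified sequence known in full, whereas the article balances on three factors. Even 10–24% needs surgeons at two hospitals to pool every allocation by stratum.
- *Concealment fails.* The next code sits in an irreversible computer system and is opened only for a consented patient in theatre. What remains is partial inference.

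The judgement exclusions are also a weak route. They are made at the first visit, about a month before the consent visit. A recruiter would have to forecast that no other patient of the same stratum, at either hospital, takes the slot first. Interventions says that the surgeons are familiar with both systems, and the section on side effects says that both prostheses are in routine use. No direction or size of bias in WOOS is shown. The two descriptions of the draw are a small mismatch, since in both the patient has consented and anaesthesia has at least begun.

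All of this stands, and it limits the size of the problem. It does not remove it: neither irreversibility nor a late draw blocks deduction from a known block length, and list order and late withholding remain open.

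**Conclusion.** The point holds as residual predictability. The block length is constant and public, unblinded surgeons draw and see each allocation, and nothing in the text counters the resulting inference. On the stratified reading, the certain share of 78 allocations ranges from about 1–4% (own cases only), through about 5% (own hospital), to 10–24% (everything in the stratum known). The result depends mostly on how much surgeons share, which the article does not address. It also rests on an assumed case mix, an assumed number of ASA levels, blocks run within strata, and known block starts; the last assumption favours the guesser. There is no evidence that anyone would use the knowledge. This is a worthwhile low-cost improvement and does not by itself make the comparison invalid.

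**What to change.** For allocations still to come:

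1. Use small, randomly varying block sizes, held by the person who builds the REDCap list and not disclosed to the sites until recruitment ends.
2. Require confirmation of eligibility in REDCap before the draw opens.
3. Reconcile the two descriptions of the draw so that the protocol gives one moment, and state who recruits and who draws.
4. Log every consented patient who is not randomised, with the reason. This would also help show whether cases were withheld.

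The cost is a new allocation table during the trial, since recruitment began on 15 April 2019, before the article appeared, plus a few protocol sentences. Overall balance becomes slightly looser if blocks of six are used; a mix of two and four only would avoid that but leave more allocations certain. Varying the blocks removes most certain predictions but lowers best-guess accuracy little. Locking a patient's place on the list just before the draw would not help, because a surgeon who predicted the arm would already have used the prediction when making the list.

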### Blinding

Patients will be blinded to which implant type they are to receive. This will be done by not sharing the operation chart files with the patient’s online file records; the inserted shoulder prosthesis will be noted by a unique code in operation file, and the radiologist will be asked not to describe the postoperative X-ray controls.

The primary investigator will conduct the blinded statistical analysis supervised by the biostatistician.

### Interventions

The operations will be performed by four shoulder surgeons familiar with the procedures of both shoulder arthroplasty systems. All patients will be operated on with the deltopectoral approach with subscapularis and biceps tenodesis and instrumentation as described by the manufacture [14].

All patients will receive standard pre- and perioperative pain management, including general anesthesia and interscalene peripheral nerve block performed by the anesthesiologist.

Postoperative pain management will be adjusted regarding each patient’s needs and recorded. We do not expect that individualized pain management will affect our primary outcome measure one year after surgery.

### Physiotherapy and self-training

All patients will receive a standardized rehabilitation program at their local municipality service. The physiotherapist in the hospital will demonstrate training protocol and instructions the day after surgery.

From 0 to 6 weeks, postoperative passive-to-active unloaded movements in all directions are allowed, with the following exceptions:No external rotation is allowed in the first three weeks. After three weeks, external rotation is allowed until the feeling of capsular tightening;No internal rotation of the operated arm behind the back is allowed in the first six weeks.

## Outcome measures

The primary outcome will be the Western Ontario Osteoarthritis Shoulder (WOOS) score at 12 months [15].

The secondary outcomes will measure the following:WOOS score at three months;OSS at 3 and 12 months postoperatively [16];General health status questionnaire EQ-5D at 3 and 12 months [17].

At baseline, three-, and twelve-month visits, patients will fill out questionnaires, WOOS, OSS, and EQ-5D, alone before leaving the hospital (at the second visit after accepting participation) and in the waiting room (at three- and twelve-month visits) without interference from the medical staff.

### Follow-up

To ensure that the prosthesis is in situ, all patients will undergo a conventional X-ray in two perpendicular views before discharge. The discharge will be on day 1 or day 2 postoperatively, depending on the patient’s pain and the need for recruiting social help service at home.

All patients will be followed actively for one year postoperatively. Further follow-up including revision rates will be recorded at five and ten years after surgery using data from the Danish Shoulder Register (DSR).

Complications and adverse events that may have developed after the 12-month evaluation but that did not lead to revision surgery will be extracted from the patient records (e.g. discharge letters, discharge diagnosis, needed journal notes).

## Outcome assessment tools

### Western Ontario Osteoarthritis of the Shoulder Score (WOOS)

The WOOS is a patient-administered, disease-specific questionnaire for the measurement of the quality of life of patients with osteoarthritis. It provides scores for four domains: (1) physical symptoms; (2) sport, recreation, and work; (3) lifestyle; and (4) emotions. Patients answer each question using the visual analogue scale. The WOOS score is calculated by measuring the distance from the left side of the line and calculating the possible score in the range of 0–100 (recorded to the nearest 0.5 mm.) It consists of 19 questions; the total score is in the range of 0–1900. A maximum score of 1900 signifies that the patient has an extreme decrease in shoulder-related quality of life, whereas a score of 0 signifies that the patient has no decrease in shoulder-related quality of life. The raw scores are converted to a percentage of the maximum score for simplicity of presentation. The questionnaire has been translated into Danish and validated and tested on patients with shoulder osteoarthritis [15, 18, 19].

### Oxford Shoulder Score (OSS)

The OSS is a measurement tool for the assessment of outcomes of shoulder surgery [16, 20]. It has been tested and validated in patients with primary or secondary osteoarthritis. The OSS is a 12-item questionnaire, with each item scored in the range of 0–4; thus, the overall score is the sum of the scores received for individual questions. This results in a continuous score ranging from 0 (most severe symptoms) to 48 (least severe symptoms) [16]. For simplicity of presentation, the raw scores will be converted to a percentage of the maximum score. We will use a validated Danish version [20].

### EQ-5D

The EQ-5D, the health status component of the EuroQol assessment (EuroQol Group, Rotterdam, The Netherlands), is a generic instrument for describing and evaluating health-related quality of life. The EuroQol instrument has been designed for self-completion by the respondent.

The EQ-5D is a descriptive system comprising five dimensions in each of which the respondents describe their health state: mobility; self-care; usual activities; pain/discomfort; and anxiety/depression. Each dimension has five levels: no problems; slight problems; moderate problems; severe problems; and extreme problems. The patients are asked to indicate their health state by ticking the box next to the most appropriate statement in each of the five dimensions, which corresponds to a one-digit number that expresses the level selected for that dimension. The patient chooses one of five levels for each dimension; thus, a five-digit number (EuroQol Group 1990) can define the resulting health state. The reliability and validity of the EQ-5D have been evaluated in different patient populations, including the Danish population, with the conclusion that the assessment had good validity, reliability, and responsiveness [17, 21]. The EQ-5D demonstrated good internal and external responsiveness in patients with shoulder injuries and can therefore be used as an outcome measure for evaluating the HRQOL in both clinical studies and healthcare assessments [22–24]. We received permission to use the Danish version (permission ID number 27296) [25].

